### Outcome measures

Table 1 shows a full summary of patient characteristics and outcome measures, including the time of collection.

**Table 1 T1:** Collection of patient characteristics and outcome measures in the RECALL trial and cohort.

	**Baseline**	**Regular care**		**Trial**							**Regular care in cohort**		
		**in cohort**									**after finishing the trial**		
	**Baseline**	**Max 90 minutes after ECT**	**Once a week during ECT** ^∧^	**Day before first ECT**	**Max 90 minutes after first ECT**	**Max 90 minutes after 2**^nd^ **ECT**	**Day after 2**^nd^ **ECT**^∧^	**Max 90 minutes after 3**^rd^ **ECT**	**Max 90 minutes after 4**^th^ **ECT**	**Day after 4**^th^ **ECT**^∧^	**Max 90 minutes after ECT**	**Once a week during ECT** ^∧^	**1 week after stop ECT**
Time	Ta	Tb		T0	T1	T2	T3	T4	T5	T6	Tb		
Socio-demographics	X												
*General clinical-demographics*													
Medical history	X												
Substance use	X												
Medication use	X	X		X	X	X		X	X	X	X		X
ATHF	X												
BMI	X												
Waist circumference	X												
Blood pressure	X												
*Physical activity and frailty*													
Frailty index	X												X
SPPB	X												X
Physical activity*	X												
Vision and hearing ability	X												
*Depression related clinical characteristics*													
BAI^a^	X												
GDS^a^	X												
AES^a^	X			X			X			X			X
MADRS^a^	X		X				X			X		X	X
CORE	X		X				X			X		X	X
*Neurocognitive characteristics*													
Battery of neuropsychological tests**	X												X
Self reported cognitive decline	X												X
IQCODE	X												X
(f)MRI	X												
EEG	X												
*Laboratory characteristics*													
Blood / urine sample	X			X									X
*Primary outcome measure*													
DRS-R-98				X	X	X	X	X	X	X			
*Secondary outcome measures*													
MMSE	X		X				X			X		X	X
Letter fluency	X			X			X			X			X
Clock Drawing Test	X			X			X			X			X
Reorientation time		X			X	X		X	X		X		
RASS		X			X	X		X	X		X		
CAM		X	X										
ECT characteristics		X			X	X		X	X		X		
Rivastigmine side-effects				X	X	X		X	X	X			

*ATHF, Antidepressant Treatment History Form; BMI, Body Mass Index; SPPB, Short Physical Performance Battery; BAI, Beck Anxiety Inventory; GDS, Geriatric Depression Scale; AES, Apathy Evaluation Scale; MADRS, Montgomery Åsberg Depression Scale; IQCODE, Informant Questionnaire on Cognitive Decline in the Elderly; DRS-R-98, Delirium Rating Scale-Revised-98; MMSE, Mini-Mental State Examination; RASS, Richmond Agitation Sedation Scale; CAM, Confusion Assessment Method*.

∧ *The day of measurement is Wednesday, as ECT is done twice weekly*.

* *Physical activity includes assessment of mobility, International Physical Activity Questionnaire (IPAQ), and self-reported activities of daily living (ADL)*.

** *Stroop Color Word Test, 15-Words Test or Auditory Verbal Learning Test, Trail making Test, Kopelman Autobiographic Memory Interview, and Visual Association Test*.

#### Primary outcome measure

During the trial, the effect of rivastigmine on inter-ictal delirium is examined through the Delirium Rating Scale-Revised-98 (DRS-R-98) (30). It was demonstrated that the DRS-R-98 is sensitive, specific, reliable, and easy to use for the assessment of severity of a delirium (30). We will compare delta-scores of the DRS-R-98 computed over the period of rivastigmine-use and placebo (T3-T0 and T6-T3, depending on whether the patients start with rivastigmine or placebo). This is assessed by a trained, blinded research nurse once weekly.

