### Sample size calculation

We estimated that in our vulnerable study population, prevalence rates of delirium and profound cognitive decline are ~20%, based on a previous study (11). In order to detect a reduction on the DRS-R-98 of 4 points (SD ± 7), at 80% power with α = 0.05, 120 delirious patients should be included in a non-cross-over trial. These patients (*n* = 120) should be identified during regular ECT (cohort study). Since the estimated prevalence of inter-ictal delirium is ~20%, the cohort should include in total at least 600–1,000 persons in order to select 120 patients. This is not possible, due to limited availability of resources. Therefore, a cross-over design will be used. A cross-over design requires fewer patients than a non-cross-over trial to achieve similar power. With an estimated correlation between intra-individual measurements of *r* = 0.50, a cross-over trial requires only 25% of the number of patients (70). Hence, a total of 30 patients provide sufficient power for the trial. With an estimated dropout of 20%, 38 patients need to be included to obtain sufficient power for the trial. We aimed at a probability of 75% to include 38 delirious patients in the trial, which would amount to 210 patients in the cohort. Eventually, with an additional 20% margin of safety due to estimated prevalence, we decided to set the inclusion goal at 250 patients for the cohort, to achieve a sample of 30 delirious patients completing the trial. However, during the first months of data-collection, the prevalence of inter-ictal delirium was noticeably higher, namely ~25%. Hence, in an amendment, the goal of inclusion in the cohort was set back to 150 patients.

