#### Data analysis

Significance will be set at *p* < 0.05 for all statistics and 95% confidence intervals will be presented. Intention to treat analyses will be conducted. Descriptive baseline statistics will be generated for the patients included in the trial. As the trial is a patient cross-over design, no comparison or correction for baseline variables will be done.

To estimate the efficacy of rivastigmine on inter-ictal delirium in the RECALL trial, delta scores of the DRS-R-98 will be used. These delta scores will be computed over the period of rivastigmine (intervention, 2 ECT sessions, 7 days) and placebo (comparison, 2 ECT sessions, 7 days) separately. For further details, see section Primary outcome measure. Analysis of Variance (ANOVA) by a mixed model for repeated measures, with treatment (rivastigmine vs. placebo) as a within effect and sequence of treatment (arm A vs. arm B) as a between factor, will be performed. Additionally, the association between rivastigmine and (delta-scores of the) DRS-R-98 will be examined in a traditional regression model, with putative effect modifiers, confounders and determinants.

Cox's regression analyses will be conducted in the RECALL cohort, with outcome defined as the (time to) occurrence of inter-ictal delirium measured by a positive CAM and/or a decline of MMSE of 4 points, adjusted for putative effect modifiers, confounders and determinants. Additionally, putative patterns of cognitive decline will be identified by data-driven methods (e.g., latent-class analysis), based on cognitive outcome measures. Future analyses in the data will depend on appropriate research questions.

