The cross-over design is chosen for three specific reasons; (1) to reduce the influence of confounding covariates, as each crossover patient serves as his or her own control; (2) to enable all trial patients to benefit from the study medication; and (3) most important, feasibility, as cross-over designs require fewer patients than non-cross-over designs to achieve sufficient power (71). The feasibility was the major argument for the design team as this is a population that is particularly hard to study. It is difficult to include patients due to less motivation which is a symptom of their disease, and—in case of legal incapability- doubts from the legal representative (e.g., family) to agree to an additional extensive battery of tests during the treatment. In addition, as in all studies on depression, we predict that the anhedonia and indecisiveness, core symptoms of depression, cause difficulties for patients to stay motivated during the entire study, resulting in missing data. The cross-over design allows this study to achieve sufficient power with 30 delirious patients completing the trial. A potential bias in cross-over designs may be “carry-over” effects. However, rivastigmine has a short elimination time [T1/2 patch = 3.4 h (72)], therefore a minimal “wash-out” period of 1 day is deemed sufficient. After removal of the patch, rivastigmine is eliminated for more than 99% within 24 h—or before the next ECT session is done. Furthermore, transdermal rivastigmine was chosen over other AChI due to reported superiority on gastro-intestinal side-effects and similar expected efficacy (73–75).

A limitation of our study is the possibly invalid use of the MMSE as an inclusion measure for patients with an inter-ictal delirium. It might be improper, as it is previously not validated as a tool for the diagnosis of inter-ictal delirium, or any other delirium (76). The same goes for the MMSE as a measure of delirium severity. However, we claim, based on our clinical experience, that inter-ictal delirium does not always behave as a “regular” delirium and therefore does not always meet the criteria for delirium as measured with the CAM. For example, hallucinations are often lacking, and the patients usually suffer from clouding of consciousness, persistent disorientation or reduced speed of processing. Hence, by screening for inter-ictal delirium using the CAM only, eligible patients for the trial might be missed.

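### The primary contrast uses T3 both as the end of period 1 and as the baseline of period 2: on the protocol's own washout premise it estimates 1.5 times the rivastigmine effect, and the sample-size factor based on r = +0.50 is not supported for it

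*Protocol article*

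**What the plan says.** All references are to the protocol article.

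- **Primary outcome measure** compares "delta-scores of the DRS-R-98 computed over the period of rivastigmine-use and placebo (T3-T0 and T6-T3", with the assignment of the two differences to treatment depending on which treatment comes first. **Data analysis** confirms that "delta scores of the DRS-R-98 will be used", computed over the "period of rivastigmine (intervention, 2 ECT sessions, 7 days) and placebo (comparison, 2 ECT sessions, 7 days) separately".
- **Table 1** lists DRS-R-98 assessments from T0 to T6. T3 is the day after the second ECT and T6 the day after the fourth. No separate DRS-R-98 baseline is scheduled for period 2.
- **Data analysis** specifies a mixed-model ANOVA "with treatment (rivastigmine vs. placebo) as a within effect and sequence of treatment (arm A vs. arm B) as a between factor".
- **Sample size calculation** sets its target as follows: "In order to detect a reduction on the DRS-R-98 of 4 points (SD ± 7), at 80% power with α = 0.05". For a parallel-group design it puts the requirement at 120 patients. It then takes a correlation of 0.50 between measurements within a person, states that "a cross-over trial requires only 25% of the number of patients", and arrives at 30 completers, or 38 with 20% dropout.
- **Discussion** sets carry-over aside on pharmacokinetic grounds: "After removal of the patch, rivastigmine is eliminated for more than 99% within 24 h".

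**The concern.** In a two-period cross-over, subtracting a baseline from each period is harmless only if that baseline is free of the other treatment's effect. Here the period 2 baseline is the on-treatment result of period 1. For a patient who takes rivastigmine first and improves, T3 is low because of the drug. When the benefit goes, T6 - T3 is positive, and the plan books that rise as deterioration under placebo. The same benefit is counted twice in one sequence and once in the other.

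Two things are at stake. The first is the scale of the headline result: readers will set the reported DRS-R-98 difference and its interval against the 4 points the trial was planned to detect. The second is the power statement: two differences that share a measurement with opposite signs tend to be negatively correlated, whereas the sample size takes credit for a positive correlation.

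**Working it through.** **Inputs.** Effect 4 points, SD 7, two-sided alpha 0.05 (sidedness is not stated, so this is an assumption), r = +0.50, 30 completers (Sample size calculation); deltas T3 - T0 and T6 - T3 (Primary outcome measure). The protocol does not say whether SD 7 and r = 0.50 refer to scores or to deltas. I assume raw scores with equal variance, 15 patients per sequence and 28 degrees of freedom. The periods are the two-session periods of Data analysis and Table 1; the treatment allocation section gives four sessions per arm, which is a separate matter to reconcile.

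**1. The plan's own figure.** Cross-over N = parallel N x (1 - r)/2 = 120 x (1 - 0.50)/2 = 30, and 30/0.8 = 37.5, rounded up to 38. Both reproduce. (The 120 itself does not follow from 4 points, SD 7 and 80% power, which give 49 per arm or 98 in total. This is a separate point, but it explains why 30 completers give more than 80% power for T3 versus T6 below.)

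**2. What the contrast estimates.** Let d be the true reduction and c the share of it still present at T6 in rivastigmine-first patients. Period effects cancel in the average over sequences and are left out.

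- Rivastigmine first: (T3 - T0) - (T6 - T3) = -d - (d - cd) = -(2 - c)d.
- Placebo first: (T6 - T3) - (T3 - T0) = -d - 0 = -d.
- Average: -(3 - c)d/2.

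Example with c = 0 and d = 4: scores of 16, 12, 16 give deltas of -4 and +4, a contrast of -8; scores of 16, 16, 12 give 0 and -4, a contrast of -4. The mean is -6.

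| c | Delta contrast, true d = 4 | Factor |
|---|---|---|
| 0 | 6 | 1.50 |
| 0.5 | 5 | 1.25 |
| 1 | 4 | 1.00 |

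A simulation with a period trend gave -5.97, -4.96 and -3.98. With d = 0 and 30 patients the contrast averaged 0.01 and the type I error was 4.9%.

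**3. Correlation of the deltas.** With equal variances, adjacent correlation r1 and T0-T6 correlation r2, corr = (2·r1 - 1 - r2) / [2(1 - r1)].

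- Equal correlations (r2 = r1): -0.5 for any r1.
- AR(1) with r1 = 0.5 (r2 = 0.25): (1 - 1 - 0.25)/1 = -0.25.
- A value of +0.50 requires r2 = 3·r1 - 2. With r1 = 0.5 that means r2 = -0.50, a degenerate case; with r1 = 0.75 it means r2 = 0.25, which is a valid correlation matrix.

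If -0.50 goes into the protocol's own formula, with SD 7 and 4 points taken on the delta scale, N = 120 x (1 + 0.5)/2 = 90 rather than 30.

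**4. Power with 30 completers.** The variance of 2·T3 - T0 - T6 is 49 x 6 x (1 - 0.5) = 147 (SD 12.1) under equal correlations and 49 x 2.5 = 122.5 (SD 11.1) under AR(1). For T3 versus T6 it is 2 x 49 x (1 - 0.5) = 49 (SD 7.0) under both. Noncentral t with 28 degrees of freedom gives:

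| Contrast | Expected value | SD | Power |
|---|---|---|---|
| Deltas, c = 0, equal correlations | 6 | 12.1 | 74% |
| Deltas, c = 0, AR(1) | 6 | 11.1 | 82% |
| T3 versus T6, c = 0 | 4 | 7.0 | 86% |
| Deltas, 4 points meant on the delta scale, equal correlations | 4 | 12.1 | 42% |
| Deltas, 4 points meant on the delta scale, AR(1) | 4 | 11.1 | 48% |

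The last two rows rest on a different premise from the first three and must not be combined with the 50% inflation.

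**The case against.** **The washout argument concerns the drug, not the symptom.** Elimination within 24 h does not show that the DRS-R-98 returns to its untreated level after a placebo week. If rivastigmine changes the course of the delirium and the gain lasts to T6, the delta contrast is unbiased. This stands. A reader might infer from the shared T3 that the trial will overstate the effect by 50% in any event; the documents do not support that. The 50% is the upper end of a 0% to 50% range. It is, however, the end that follows from the protocol's own reason for dismissing carry-over.

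**A positive correlation is possible.** A reader might also infer that the deltas cannot correlate at +0.50. That is not so: strong patient-specific trends can produce it, as the 0.75/0.25 matrix shows. But the protocol argues for no such pattern, and it attaches 0.50 to measurements, not to deltas. The supportable statement is that the factor is not justified for this outcome.

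**The test is valid, and the inflation buys back power.** Both are correct. Under no effect the contrast centres on zero. On the premise that creates the inflation, power is 74% to 82% against a planned 80%, so it would be wrong to read the trial as hopelessly underpowered.

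**T3 versus T6 has its own bias.** It estimates (1 - c/2) of the effect: 3 points at c = 0.5 and 2 at c = 1, for a true 4. Under equal correlations its power is 86%, 62% and 33% at c = 0, 0.5 and 1, against 74%, 59% and 42% for the deltas. This stands, and the fix has to state it.

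**A missing T3** removes both deltas, but it equally removes the within-patient T3 - T6 difference, so it does not favour either contrast.

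**Conclusion.** The point holds in a conditional form. The primary contrast reuses T3 with opposite sign. If the effect reverses by T6, as the Discussion's washout argument implies, the contrast estimates 1.5 times the effect and a true 4 points appears as 6; the factor falls linearly to 1 as the persisting share c rises from 0 to 1. What is affected is the size of the estimate and its confidence interval, not the validity of the test of no effect.

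Separately, the 25% factor describes a contrast with r = +0.50, whereas the planned deltas correlate at -0.5 (equal correlations) or -0.25 (AR(1) with r = 0.5). With SD 7 and r = 0.5 on raw scores, 30 completers give 74% to 82% power for a fully reversing 4-point effect, against 86% for T3 versus T6. If instead the 4 points were meant on the delta scale, power is about 42% to 48%. The stated sample size therefore fits an end-of-period contrast better than the one specified.

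**What to change.** By dated amendment, before any unblinded analysis:

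1. Make the primary contrast the within-patient difference in end-of-period DRS-R-98, T3 versus T6, with treatment, period and sequence in the model.
2. Report the first-period comparison (T3 adjusted for T0) as a supportive check. It is free of carry-over, but with about 15 against 15 patients it has low power and cannot rule out persistence.
3. Restate the power for the contrast actually analysed, saying whether SD 7, r = 0.50 and the 4 points refer to scores or to differences.

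**Cost.** No new data are needed, since T0, T3 and T6 are already scheduled. Recruitment had begun and patients are unblinded after their treatment period, so the change has to be documented and dated, not just reworded. The statistical price is attenuation to (1 - c/2) of the effect if a share c persists. The gain therefore depends on the no-carry-over assumption that the protocol itself makes, and the amendment should say so.

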### Secondary outcome measures

Additional cognitive function tests are used to further specify the cognitive deficits, namely the Mini Mental State Examination (26) (MMSE), letter fluency or Controlled Oral Word Association Test-FAS (31), the Clock Drawing Test (32), reorientation time (33, 34), the Richmond Agitation Sedation Scale (35) (RASS) and the Confusion Assessment method (25) (CAM). The MMSE is a screening instrument for measuring the severity of cognitive impairment with good interrater and test-retest reliability (25). The Controlled Oral Word Association Test (COWAT) is widely used in clinical neuropsychology and is a measure of language and executive function. The patient is asked to name as many words as possible with the assigned letter. Patients cannot use names or numbers and cannot use words with different tenses or endings once the root word has been given. Psychometric properties were similar in the Dutch-version as compared to the original version, with reliability-scores of 0.8 (31). The COWAT is specifically chosen as an addition to the MMSE to test executive functioning. The Clock-Drawing Test (CDT) is another widely used cognitive screening tool of executive function, visuospatial abilities, motor execution, attention, language comprehension, and numerical knowledge, with good reliability and validity in patients with cognitive impairment (36). Patients are verbally asked to draw an analog clock, including all of the numbers, and set to a specified time (e.g., 10 min past 11 am). In order to diminish a learning effect of repetitive cognitive testing, the three-word recall test (included in the MMSE) and letter fluency differs in consecutive sessions. The early reorientation time—or postictal orientation recovery time—is the time until reorientation directly post-ECT, until a maximum of 90 min. It is a continuous assessment by the research nurse, asking the patient to state his / her name, location, age, date of birth and the day of the week. Four correct answers out of five questions is considered as adequate orientation (34). When unable to answer correctly within 90 min, a score of 100 min will be noted. The reorientation time is an easy test to administer. Duration of postictal reorientation has been associated with the extent of retrograde amnesia in the past (34). Sedation or agitation status is assessed by the Richmond Agitation Sedation Scale (RASS) (35). The RASS has excellent interrater reliability and criterion-, construct-, and face validity (37). It takes around 30 s to administer. The Confusion Assessment Method is used as an outcome measure in the cohort to define the amount of patients with a probable delirium in the cohort. It takes ~2 min to administer. For a diagnosis of delirium by CAM, the patient must display: (1) presence of acute onset and fluctuating discourse, and (2) inattention, and either (3) disorganized thinking or (4) altered level of consciousness. The CAM has good sensitivity (94–100%) and specificity (90–95%) and the interobserver reliability rates are high (0.81–1.00) (25).

Furthermore, in order to investigate the safety and effect of rivastigmine on ECT-parameters and anesthesia, we measure blood pressure, peak heart rate, seizure length (EEG and motor duration in seconds), postictal suppression index (in %) and seizure threshold. Apart from the postictal suppression index and seizure length measured by the Thymatron IV (unavailable at sites with the spECTrum), all variables are recorded by a blinded anesthesiologist. Next, side-effects of rivastigmine are evaluated twice weekly (by a research assistant) using a four-point side-effects scale with the five most common side-effects of rivastigmine (nausea, vomiting, diarrhea, abdominal pain, allergic skin reaction), and an open question for additional side-effects.

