### Study population and inclusion criteria

In- and outpatients, aged 55 years or older, fulfilling the Composite International Diagnostic Interview CIDI) criteria of a Major Depressive Episode—in the context of a unipolar major depressive disorder or bipolar disorder- and referred for ECT-treatment, are asked to participate in the cohort and, in case of occurrence of inter-ictal delirium, in the trial (22–24). Before inclusion, they provide a written informed consent form. The presence of an inter-ictal delirium is examined with the Confusion Assessment Method (25) (CAM) and/or Mini Mental State Examination (26) (MMSE), administered by a trained research assistant. For a diagnosis of inter-ictal delirium, patients need to have a CAM score indicating delirium or a drop in MMSE-score of at least 4 points as compared to baseline. The evaluation of inter-ictal delirium was done during regular screening once weekly, preferably in the middle of a week, 1 day (and maximum 2 days) after ECT. This timing was chosen to (1) select persistent cases of delirium, and hence not to include mild disorientation or transient delirious episodes immediately post-ECT; (2) to increase feasibility by avoiding cognitive testing during weekends and (3) to diminish the learning effect of repeated cognitive testing. Once delirium was diagnosed, an evaluation was done by the clinician to indicate whether it was needed to further exclude possible causes of delirium.

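### A positive CAM is enough on its own for trial entry and for the cohort's Cox event, but no CAM is scheduled at baseline, so that half of the delirium definition is not verified as new after ECT

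*Protocol article*

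**What the plan says.** Under Study population and inclusion criteria, for inter-ictal delirium "patients need to have a CAM score indicating delirium or a drop in MMSE-score of at least 4 points as compared to baseline". Under Data analysis, the Cox model in the cohort takes as its outcome the time to "occurrence of inter-ictal delirium measured by a positive CAM and/or a decline of MMSE of 4 points". Either criterion is sufficient in both places.

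Under Secondary outcome measures, the CAM "is used as an outcome measure in the cohort to define the amount of patients with a probable delirium". A positive result requires, among other features, "1) presence of acute onset and fluctuating discourse, and (2) inattention". Of its burden the article says: "It takes ~2 min to administer".

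Table 1, which the article presents as the complete overview of measures and their timing, marks the CAM in two columns only: within 90 minutes after ECT, and weekly during ECT, both in the cohort phase before the trial. The baseline column (Ta) is blank for the CAM. The MMSE is marked at baseline.

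The Discussion says that because determinants are measured at baseline, their association with the onset of inter-ictal delirium can be studied.

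**The concern.** A time-to-onset analysis needs each patient to be event-free at time zero. For the MMSE criterion this holds by construction, because the event is a fall from the patient's own baseline. For the CAM criterion nothing in the schedule shows it. A patient who was CAM-positive before the first ECT session, and still is at the first weekly screen, would enter the Cox model as an early ECT-induced event and could be offered the trial on the same footing.

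What is at stake is mainly the cohort analysis. Prevalent cases counted as incident ones pull the estimated determinants of onset toward determinants of delirium that was there already, and they cluster at the earliest event times. For the trial, the consequence is a less certain description of who was randomised.

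**Working it through.** The article has no figure of its own on this point to reproduce. The check is a reading of the Table 1 rows against the definitions, followed by an illustration of size.

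**Schedule.**

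| Instrument | Baseline Ta | Weekly in cohort before trial | T0 | T3 | T6 |
|---|---|---|---|---|---|
| CAM | no | yes | no | no | no |
| MMSE | yes | yes | no | yes | yes |
| DRS-R-98 | no | no | yes | yes | yes |

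The CAM is also marked within 90 minutes after ECT in the cohort phase, and the DRS-R-98 at the remaining trial visits. T0 is headed as the day before the first ECT, but it stands under the Trial heading. It therefore precedes the first trial session and follows the positive screen; it is not a pre-ECT measurement.

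**Does anything else establish CAM-negative status before ECT?**

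- Cohort exclusions cover a diagnosed neurocognitive disorder. Delirium present before ECT is not named.
- The DRS-R-98 is not done at Ta.
- The baseline EEG, which the article says can pick up signs of delirium, is limited to consenting patients from two of the four sites.
- The acute-onset feature of the CAM does not place the onset after the first ECT session.

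So the MMSE criterion has a baseline reference in every patient, and the CAM criterion has none.

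**Illustration of size.** Inputs from Sample size calculation: amended cohort goal 150; observed prevalence of inter-ictal delirium about 25%. Assumed, because the article does not give it: baseline CAM-positive rate p of 2%, 5% or 8%.

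- Expected events: 150 × 0.25 = 37.5.
- Prevalent cases: 150 × p.
- Share of events: (150 × p) / 37.5.

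| Assumed p | Prevalent cases | Share of 37.5 events |
|---|---|---|
| 2% | 3 | 8% |
| 5% | 7.5 | 20% |
| 8% | 12 | 32% |

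The calculation takes the 25% to refer to the same CAM-or-MMSE definition, so that prevalent cases sit inside the 37.5. It also assumes that every baseline-positive patient is still positive at a later screen and that none would have had a genuine ECT-induced event anyway. Each figure is therefore an upper bound at its assumed rate.

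**The case against.** The strongest reply is that the plan has several safeguards. Events by the MMSE route are already anchored to baseline. A positive CAM needs acute onset. After a positive screen a clinician judges whether other causes must be ruled out, and patients with an identified physical cause other than ECT are kept out of the trial. The baseline visit also includes medical history, neuropsychological tests and the IQCODE. This stands in part: a reader might infer that new and pre-existing delirium cannot be told apart at all, and the article does not support that. But the physical-cause exclusion applies to the trial and not to the cohort. The clinician's evaluation comes after the positive screen, when the patient's CAM status before ECT can no longer be measured. The safeguards reduce the problem without closing it for the CAM route.

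A reader might also infer from the blank CAM cells at T3 and T6 that the trial has lost an outcome it needs. It has not. The stated trial outcome is severity: "We will compare delta-scores of the DRS-R-98 computed over the period of rivastigmine-use and placebo". No resolution endpoint is promised, and the CAM is assigned to the cohort. DRS-R-98 and MMSE are both taken at T3 and T6. A proportion no longer CAM-positive would be undefined for patients who entered on the MMSE alone, and the Discussion expects such patients. The absence of the CAM at T3 and T6 is not a defect.

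Finally, the 2% to 8% range has no source in the article. That is correct, and the resulting shares should not be read as estimates.

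**Conclusion.** The point holds in a limited form. The CAM is one of two sufficient criteria for trial entry and for the Cox event. Unlike the MMSE drop, it has no baseline reference, so followed as written the schedule allows prevalent CAM-positive patients to be counted as incident. The size is unknown. At assumed baseline rates of 2%, 5% or 8% it is at most 3, 7.5 or 12 of about 37.5 expected events, and it could be close to none.

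The effect is on the onset analysis in the cohort and on the description of trial entrants. It does not extend to the primary trial analysis, which compares DRS-R-98 changes within patients and does not use the CAM. This is an inexpensive improvement and not a fault that threatens the trial.

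**What to change.** 1. Add the CAM to the baseline column (Ta) of Table 1.
2. State in Data analysis that patients CAM-positive at baseline are left out of the Cox risk set, or alternatively that only their MMSE-defined events count.
3. Flag baseline-CAM-positive patients at trial entry, so that their number can be reported.
4. Data collection has begun, and a baseline CAM cannot be recovered for patients already enrolled. For them, specify a sensitivity analysis that drops events resting on the CAM alone at the first weekly screen, and report the limitation. That analysis is deliberately strict: it will also remove some genuine early events.

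The cost is an amendment to the schedule and about 2 minutes at a visit that already takes place and already includes the MMSE. A few patients would leave the risk set: 3 to 12 of 150 at the assumed rates, fewer if the MMSE-only alternative is used. No change to T3, T6 or the primary analysis is needed.
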